At delivery, the transplant is thawed and 0.5 mL representing 3.5 mg of the mother’s fecal sample is dissolved in 5 mL of the mother’s own milk or when not available pasteurized bank milk. The sample is given orally to newborn infants born to *GI (Intervention group)* mothers within 2 h of delivery. The newborn infants born to *GP* (*Placebo group)* mothers are given 0.5 mL of isotonic saline dissolved in 5 mL of pasteurized bank milk or mother’s own milk as described earlier. The randomization is performed on the day of the scheduled CS and 0.5 mL of either transplant or placebo is delivered to the ward on ice in a black polypropylene tube for blinding purposes.

Infant exclusion criteria are Apgar score of less than 8 at 5 min of age, birth weight below 2500 g or above 4500 g, disturbances of neonatal adaptation (such as transient tachypnea of the newborn) and antibiotic treatment of the newborn before discharge. In case of a suspected infection of the newborn the randomization code can be opened.

After the first feeding the newborn is observed for potential reactions, such as increased peristalsis, diarrhea, vomiting, fever, and rash. Possible adverse events are reported to the electronic database. Before discharge, typically on postnatal day 2, a 3 mL blood sample is gathered from the newborn for the assessment of white cell count, C-Reactive Protein (CRP) and hemoglobin, and for detailed immunological analyses. The sample is taken at the routine sampling for metabolic screening.

During the hospital stay two fecal samples are collected from the newborn: on the day of birth and third day of life (Fig. 1).

From the first postnatal week on, the infant is followed in the well-baby clinic according to national protocols. As a part of the study, the parents can be in contact with the study nurse and pediatrician by telephone. Fecal samples of the infant are taken weekly for the first 4 weeks, and at 8 weeks and 3 months, by the parents. Fecal sample from the mother is taken 4 weeks postpartum. Samples are temporarily stored at − 20 °C in the home freezer before transfer in frozen form to − 80 °C. (Fig. 1).

Breastfeeding mothers give a breast milk sample at 2 and 8 weeks postpartum. Milk samples are temporarily stored at − 20 °C in the home freezer before transfer in frozen form to − 80 °C.

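### Antibiotic treatment before discharge is an infant exclusion criterion, although it is mostly a post-randomisation, post-dose event that the transplant could influence

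*Protocol article*

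**What the plan says.** All the relevant text is in the protocol article, Study design, in the paragraphs after Table 1.

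- Randomisation: "The randomization is performed on the day of the scheduled CS". The transplant or placebo then goes to the ward and is fed within 2 h of delivery.
- Infant exclusions: low Apgar score, birth weight outside a range, disturbed neonatal adaptation and, with the code-break provision directly after it, "antibiotic treatment of the newborn before discharge. In case of a suspected infection of the newborn the randomization code can be opened".
- Observation after the first feeding covers "potential reactions, such as increased peristalsis, diarrhea, vomiting, fever, and rash". Possible adverse events are entered in the electronic database.
- Discharge: "Before discharge, typically on postnatal day 2, a 3 mL blood sample is gathered from the newborn". The sample is used "for the assessment of white cell count, C-Reactive Protein (CRP) and hemoglobin", and for immunological analyses.

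The Outcome section compares the two groups on the microbiome at 3 months. The Power analysis section expects 60 infants, 30 per arm, after a 40% loss to maternal screening. It mentions follow-up drop-outs without a number and gives no figure for infants excluded after birth. Nothing in the article says that an infant excluded for antibiotics stays in follow-up, in the primary comparison or in a safety table.

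**The concern.** An exclusion criterion protects a randomised comparison when it rests on facts that the treatment cannot change. Antibiotic treatment in the first two days of life mostly fails that test here. It generally comes after the infant has received either live maternal fecal material or saline, and fever or suspected infection after the feeding could lead to it. Removing infants on that basis leaves two groups that may no longer be comparable. The permitted code break adds a second route, since a decision to treat, and with it the exclusion, could be taken by someone who knows the allocation.

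Two things are at stake. The first is the primary comparison. The Background section describes infant stool communities as following similar trajectories when no antibiotics are given, so by the article's own account the excluded infants may differ on the outcome. The second is safety: suspected early infection is an event that this trial should be able to compare by arm, and with 30 infants per arm each case counts.

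**Working it through.** **Timing.** Putting the statements in order:

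1. Randomisation on the day of the section.
2. Dosing within 2 h of delivery.
3. Observation for fever and other reactions.
4. Blood sample, then discharge, typically on day 2.

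The antibiotic criterion runs from birth to step 4. At most the first 2 h precede the dose; the rest follow it. Apgar score at 5 min and birth weight may also become known after randomisation, but they precede dosing and the transplant cannot cause them.

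**The plan's own numbers.** 100 × (1 − 0.40) = 60 reproduces the planned size. That 40% is maternal screening, before randomisation. There is no planned antibiotic rate to reproduce, so what follows is illustration on assumed rates.

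**Infants lost (assumed rates).** Expected exclusions = 30 × rate.

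- Placebo, 2% to 5%: 30 × 0.02 = 0.6 to 30 × 0.05 = 1.5.
- FMT, 10% to 20%: 30 × 0.10 = 3 to 30 × 0.20 = 6.

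**Shift between arms with no true effect.** Suppose that infants with the highest infection liability are treated and excluded, and that liability has correlation ρ with the outcome (assumed 0.3 to 0.5). Excluding a fraction p lowers the mean liability of those retained by m(p) = φ(z₁₋ₚ)/(1 − p):

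- m(0.02) = 0.0484/0.98 = 0.049
- m(0.05) = 0.1031/0.95 = 0.109
- m(0.10) = 0.1755/0.90 = 0.195
- m(0.20) = 0.2800/0.80 = 0.350

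The size of the shift is ρ × [m(p_FMT) − m(p_placebo)], in SD:

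| Placebo, FMT rate | ρ = 0.3 | ρ = 0.5 |
|---|---|---|
| 5%, 5% | 0 | 0 |
| 5%, 10% | 0.026 | 0.043 |
| 2%, 10% | 0.044 | 0.073 |
| 5%, 20% | 0.072 | 0.121 |

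The range for unequal rates is about 0.03 to 0.12 SD. Exchanging the two rates reverses the sign. Equal rates give no shift here only because the model lets the same type of infant be treated in both arms.

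**Safety (hypothetical count).** If 3 of 30 FMT infants had treated infections, the rate would be 10%, with a two-sided 95% Clopper-Pearson interval of 2.1% to 26.5%. If all three were excluded and the table covered retained infants only, it would show 0/27, with a two-sided 95% upper limit of 1 − 0.025^(1/27) = 12.8%.

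**The case against.** Much of the opposing case is fair.

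- **Safety events are not deleted.** A reader might infer that the rule removes the key safety events from the trial. The article does not say so: adverse events are reported to the electronic database. What it leaves open is whether excluded infants remain in follow-up and in the by-arm comparison. This stands.
- **Bias is possible, not shown.** The criterion applies to both arms, and no rates are given. A reader might also infer that the rule favours FMT, but the direction is open. The Background says that caesarean delivery and maternal antibiotic prophylaxis predispose infants to opportunistic pathogens, so placebo infants might be the ones excluded more often. The pilot of seven treated infants reported no adverse effects over 3 months; that is too few to rule out harm, but it lends no support to a high FMT rate. This stands.
- **A large share of the target effect cannot be claimed.** A reader might take 10% to 20% of FMT infants as excluded and 1 SD worse, obtain 0.10 to 0.20 SD, and set that against the 0.25 SD in the Power analysis section, giving 40% to 80%. This assumes no placebo exclusions, a 1 SD deficit with no source, and one reading of 0.25. If 0.25 is Cohen's f, the two-group difference is 0.5 SD and the share halves. That yardstick is itself unsound: 15 per group gives about 26% power for two groups with f = 0.25, or 10% two-sided with d = 0.25, not the stated 85%.
- **Two links are inferred.** The article does not say that the pre-discharge CRP triggers antibiotics, nor that the code is opened before the decision to treat. Both are possible; neither is stated.
- **The exclusion has a rationale.** The aim is partly mechanistic and antibiotics disturb the microbiota. That supports an antibiotic-free analysis as a supporting one, but it does not justify defining the randomised comparison by a post-dose event.
- **Analysis sets may be defined elsewhere.** A SAP or full protocol, not shown, may do this. But the exclusion is a rule stated in the article, not a detail left out of it.

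**Conclusion.** The point holds as a flaw in a stated rule. The criterion is mostly a post-randomisation, post-dose event that the transplant could influence and that might be applied with knowledge of allocation. It can bias the 3-month comparison if early antibiotic use, or the type of infant treated, differs by arm. It may also take these infants out of follow-up and out of the by-arm safety comparison.

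The timing rests on the text alone. The size does not: 0.03 to 0.12 SD depends on assumed antibiotic rates and an assumed correlation, and the true size and direction are unknown. Antibiotics started before the dose, within the 2 h window, fall outside the criticism.

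**What to change.** - Limit infant exclusions to facts fixed before the product is given. Antibiotics started before the dose can remain among them.
- Keep every randomised and dosed infant in follow-up, in the primary analysis as randomised, and in all safety tables.
- Record antibiotic treatment after the dose and before discharge as an outcome. Report it by arm, together with suspected infection and code breaks.
- Show the analysis without antibiotic-treated infants as a sensitivity analysis only, labelled as conditioning on a post-dose event.

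The cost is a change of wording, follow-up of a few more infants, and slightly more variability in the primary outcome from antibiotic-exposed infants. No change to clinical management or to the code-break rule is implied.

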## Methods

### Fecal samples

The maternal transplant is prepared from a fresh fecal sample taken at least one week before elective CS and within 6 h of donation prepared as described [32], and frozen at -80C.

For the follow-up samples, a home sampling kit is provided for fecal samples of the mother and of the infant’s feces from diapers. The intestinal microbiota of mothers and infants is determined using 16S rRNA gene amplicon sequencing using the MiSeq sequencing [22, 23]. Fecal DNA is extracted by repeated bead beating from ca. 125 mg of fecal material [33] and processed for sequencing of the hypervariable V3-V4 region of the 16S rRNA gene using primers 341F 5′-CCTACGGGNGGCWGCAG-3′ and 785R 5’-GACTACHVGGGTATCTAATCC-3′ [15, 34] and barcoding primers from Kozich et al. [35] as explained in detail elsewhere [36]. The pooled libraries are sequenced with Illumina MiSeq platform using a MiSeq v3 reagent kit (MS-102–3003) with 5% PhiX as spike-in (Illumina).

The DNA sequences are processed and analyzed using the R-package mare [37, 38], which uses USEARCH and ASVs for read processing, and taxonomic annotation [39]. DNA extractions and MiSeq runs are processed in a time frame of 12 months and include internal reference samples and, if requested, a mock community [40, 41]. Metagenomic analysis is conducted essentially as previously demonstrated [42]. In brief, Nextera XT libraries are sequenced with Illumina Novaseq with the target of 7 Gbp of sequence per sample at the sequencing laboratory of the Institute for Molecular Medicine Finland FIMM Technology Centre, University of Helsinki. Filtered reads are assembled with Metaspades and Megahit and ORFs are predicted with Prodigal. Species level community profiling based on marker genes are done using Metaxa2. Resistance genes are characterized by mapping metagenomic reads with Bowtie2 against the CARD and Resfinder databases to search for acquired antibiotic resistance genes [42].

### Blood samples

We collect 1.5–5 mL of blood from the children depending on their age. For mass cytometry analysis, 100 μL whole blood is mixed with Whole Blood Cell Stabilizer (Cytodelics AB, Stockholm, Sweden) at a ratio of 1:1, incubated at room temperature for 10 min and transferred to a − 80 °C freezer for storage (6–9 months as per the manufacturer’s recommendation) until further processing for mass cytometry experimentation [2].

For fix/lysis of stabilized and cryopreserved whole blood sample, 100 μL sample is thawed at 37 °C followed by addition of Fix/Lyse buffer (Cytodelics AB, Stockholm, Sweden) at a blood:buffer concentration of 1:10 and incubated at room temperature for 10 min. The sample is then diluted 1:4 with Wash buffer #1 (Cytodelics AB,Stockholm, Sweden) and left to lyse for 15 min at ambient temperature. Cells are then washed twice with Wash buffer #2 (Cytodelics AB, Stockholm, Sweden), filtered through a 35 μm mesh and counted using a Bio-Rad TC20 cell counter [2].

Peripheral blood mononuclear cells (PBMC) are isolated using density gradient-based separation. 300–500 µL of blood is put in a BD Vacutainer CPT tube and centrifuged at 1600xg for 15 min followed by collection of buffy coat. Cells are frozen in freezing medium containing 50% RPMI, 30% FBS and 20% DMSO and processed as described previously [2] and transferred to a − 80 °C freezer for long-term storage awaiting analysis.

Plasma samples are obtained by centrifugation of blood samples at 2000xg for 10 min at 8–12 °C and supernatant collected and processed as described previously [2]. The samples are frozen at -80 °C post collection. Plasma protein analyses are done using Olink’s PEA assay (Olink, Uppsala, Sweden).

Humoral vaccine responses are measured at the age of 12 and 24 months as follows: concentrations of serum IgG to pneumococcal capsule polysaccharides included in the 10-valent PCV (1, 4, 5, 6B, 7F, 9 V, 14, 18C, 19F and 23F) and *Haemophilus influenzae* type b capsule polysaccharide are measured from serum samples with a fluorescent bead-based multiplex immunoassay (Luminex) as described previously [43].

Assessment of allergen-specific IgEs are analyzed with Immuno-CAP (Phadia, Uppsala, Sweden) in blood samples collected at the 12 and 24 months visits at the Laboratory of Helsinki University Hospital as described earlier [44].

### Breast milk

The samples are collected 2 and 8 weeks post-partum from breast feeding mothers. FUT2 dependent milk oligosaccharides are analyzed as described earlier [23]. In essence, skimmed breast milk samples are analyzed using MALDI-TOF (matrix assisted laser desorption/ionization—time of flight) mass spectrometry (MS) profiling and liquid chromatography to quantify 2′fucosyllactose (2′FL) and by high performance anion exchange chromatography (HPAEC) with a CarboPac PA1 analytical column coupled to a pulsed amperometry detector (ICS3000, Thermo Fischer Dionex, Sunnyvale, USA).

### Questionnaires

Data are collected on the families’ lifestyle, environmental exposures and the health of the study infants and their parents using online questionnaires, enabling monitoring and data query during data collection. Questionnaires are filled by the parents before the birth of the infant and subsequently. Parents are requested to fill in questionnaires on child’s nutrition, gastrointestinal function, and care practices weekly for the first 3 months, then monthly until 12 months of age and then at 18 months and 24 months of age. The questions change as the child grows. Illnesses, medication and use of probiotics and other dietary supplements are reported in the questionnaires. The questionnaires related to nutrition, health and background are mainly similar as in the ongoing HELMi study [45]. To enhance compliance of response rates to the questionnaire, parents receive automatic reminders via email and SMS-messages.

## Outcome

### Microbiome

The primary outcome of the study is the difference in composition of the intestinal microbiome, specifically diversity and relative abundances of Bacteroides spp., Bifidobacterium spp. as well as known pathobionts between the two groups at 3 months of age. We use beta-diversity between the microbiota profiles of the two groups calculated by PERMANOVA as described previously [46]. The analysis of the gut microbiome is performed at 12 months (including previous sequential samples) and at 24 months. Unblinding for the parents is done at 12 months and for the research group at 24 months.

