### Power analysis

The trial is designed with a planned sample of 100 mothers, allowing the final number of the subjects with an estimated 40% drop-out rate due to screening positivity to be 60 (30 in each intervention group) taking into consideration that it is likely to have drop-outs during the follow-up period.

Heterogeneity of microbiota is calculated as an index and used as the primary outcome at 3 months of age. The Standard Benjamini–Hochberg corrections for multiple testing are applied when testing multiple taxa. FDR-corrected *p*-values < 0.15 are considered statistically significant, but if needed uncorrected *p*-values are reported for clarity. 15 infants per CS group would be sufficient to detect a moderate effect size of 0.25 standard deviations for our primary outcome (power calculation for balanced one-way ANOVA test, 85% power, α = 0.05).

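### The 3-month primary outcome is defined in two different, unreconciled ways, and no rule says which measure decides the trial

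*Protocol article*

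**What the plan says.** The Microbiome subsection under Outcome defines the primary outcome first as a set of measures: "The primary outcome of the study is the difference in composition of the intestinal microbiome, specifically diversity and relative abundances of Bacteroides spp". Bifidobacterium is then added, and the sentence ends with a group that is not listed: "as well as known pathobionts between the two groups at 3 months of age". The next sentence gives the method: "We use beta-diversity between the microbiota profiles of the two groups calculated by PERMANOVA as described previously".

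The Power analysis subsection gives another definition for the same time point: "Heterogeneity of microbiota is calculated as an index and used as the primary outcome at 3 months of age". The index is not named. The rule for multiplicity is limited to taxa: "corrections for multiple testing are applied when testing multiple taxa", with FDR-corrected "values < 0.15 are considered statistically significant". Uncorrected p-values may also be reported where needed. The sample size for the primary outcome rests on a "power calculation for balanced one-way ANOVA test, 85% power, α = 0.05".

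The Microbiome subsection also sets the timing. The microbiome is analysed at 12 months, with the earlier samples included, and again at 24 months. The research group is unblinded at 24 months.

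**The concern.** The two subsections describe different variables that need different tests. A PERMANOVA on a distance matrix asks whether whole profiles differ between arms. It does not test the abundance of any named taxon. A scalar index compared by ANOVA asks whether one summary number differs. Taxon-by-taxon tests are a third family with their own threshold. These can disagree: Bacteroides may rise in the transplant arm while a heterogeneity index does not move.

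The article does not say which result then answers the primary question, or whether several must agree. Two things are at stake. The choice could be made after the results are known, and the error rate of the primary claim is not fixed by the text.

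**Working it through.** **1. The definitions side by side (all at 3 months)**

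| Where | Variable | Test | Threshold |
|---|---|---|---|
| Outcome, Microbiome, first sentence | Diversity; Bacteroides; Bifidobacterium; unlisted pathobionts | Not named there | Taxa: FDR < 0.15 (from Power analysis) |
| Outcome, Microbiome, next sentence | Beta-diversity | PERMANOVA | Not stated |
| Power analysis | One unnamed heterogeneity index | One-way ANOVA, in the power statement only | α = 0.05, in the power statement only |

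No sentence ranks these rows or says how they combine. The only correction covers multiple taxa. It does not reach across index, PERMANOVA, diversity and taxa.

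**2. Does the power statement show which measure was meant?**

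The stated figure is 15 infants per group, 0.25 SD, 85% power, α = 0.05. For two groups the noncentral F has noncentrality 2·n·f², with f = d/2.
- 0.25 read as a mean difference in SDs: f = 0.125, noncentrality 2·15·0.015625 = 0.47, power about 0.10.
- 0.25 read as Cohen's f: noncentrality 2·15·0.0625 = 1.88, power about 0.26.

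Neither gives 0.85, so the figure cannot be used to infer the intended outcome. That failure is a separate matter from the present point. As a test, ANOVA could fit the scalar index. It does not cover the PERMANOVA or the taxon tests.

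**3. Error rate under each possible decision rule (no true difference)**

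*All components must be positive.* The chance of a false claim is at most that of the strictest component, hence at most 0.05.

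*Any one component suffices.* Assume k independent tests at 0.05, plus a taxa family under Benjamini–Hochberg at 0.15. With all taxa null and independent, that family gives at least one false rejection with probability 0.15. Then P(any false claim) = 1 − 0.95^k × 0.85:
- k = 1 (diversity, beta-diversity and index are one measure): 1 − 0.95 × 0.85 = 0.193
- k = 2: 1 − 0.9025 × 0.85 = 0.233
- k = 3 (three separate measures): 1 − 0.857375 × 0.85 = 0.271

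Without the taxa, three independent tests give 1 − 0.857375 = 0.143.

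**4. Effect of correlation**

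All measures come from the same stool profiles, so independence overstates the totals. The 0.15 for the taxa family also falls. Simulated two-sided, equicorrelated z-tests under the global null at q = 0.15 gave P(any rejection) of about 13% (5 taxa) and 12% (10 taxa) at correlation 0.5. At correlation 0.8 it was about 10% and 9%. So 15% is not a floor, but in these settings the taxa family alone stays above 5%.

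**The case against.** The strongest defence is that this is loose wording for one construct. The Outcome section mentions diversity and then says that beta-diversity is used, which may specify it. The Study purpose subsection frames the aim as heterogeneity of the microbiota, the same word as in the Power analysis. An ANOVA on a scalar index is coherent. Details such as the distance, the taxonomic level, the index formula and the list of pathobionts are commonly left to the full protocol or the statistical analysis plan, and the PERMANOVA method is referred to a cited source.

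Much of this stands. The definitions could coexist if one were named as deciding, and the missing details alone would be no finding. But a PERMANOVA on distances and a single index per infant are not the same analysis, and the named taxa sit inside the primary outcome in one subsection and not in the other. An analysis plan could settle this only by overriding one of the two statements.

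Three stronger readings are tempting and are not supported:
- A reader might infer that the trial succeeds if any version is significant. No such rule is written. If all had to agree, the false-positive rate would be 5% or less.
- A reader might infer that the power calculation matches no stated outcome. It can apply to the index, though the article does not say so outright.
- A reader might take 27% as the error rate or 15% as its minimum. The first needs independence and three separate tests at 0.05 that the text does not set out. The second fails when taxa are correlated.

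**Conclusion.** The point holds as a contradiction within the article: two definitions of the primary outcome at one time point, two significance rules, and no statement of which measure decides. The consequence that follows directly is that the primary result could be selected after the data are seen.

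The inflation of the error rate is conditional. It arises only if one positive component were enough. It then runs illustratively from about 19% to 27%, assuming one to three independent tests at 0.05 and an independent taxa family at FDR 0.15, and it is lower with correlation. This should be corrected before group results exist, because the main question now has no single defined answer.

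**What to change.** Reconcile the Microbiome and Power analysis subsections by naming one deciding analysis of the 3-month infant sample at α = 0.05, two-sided where the test has a direction. Either choice is defensible:
- PERMANOVA of arm on one stated distance, or
- a heterogeneity index that is named and defined, with its test.

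Make the remaining diversity measures, Bacteroides, Bifidobacterium and a closed list of pathobionts secondary, under FDR control. Restate the power for the chosen test, with its effect-size measure and number of groups.

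The deadline is before any by-group microbiome analysis. Unblinding of the research group at 24 months is too late a marker, because the analysis scheduled at 12 months already takes in the 3-month samples.

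The cost is wording in the protocol and analysis plan, plus a new power calculation. The price is that the other measures lose primary status.
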